## Abstract

**Background:**

An extreme and persistent dysbiosis occurs among critically ill patients, regardless of the heterogeneity of disease. Dysbiosis in critically ill patients may make them prone to hospital-acquired infections, sepsis, multi-organ failure (MOF), energy homeostasis disturbance, muscle wasting, and cachexia. Modulation of gut microbiota through synbiotics can be considered as a potential treatment for muscle wasting and macronutrient homeostasis disturbances.

**Methods:**

This is a prospective, single-center, double-blind, parallel randomized controlled trial with the aim to evaluate the effects of synbiotic supplementation on energy and macronutrient homeostasis and muscle wasting in critically ill patients. A total of 40 hemodynamically stable, adult, critically ill patients who receive enteral nutrition via a nasogasteric tube (NGT) in the 24–48 h after admission to critical care will be included in this study. Eligible patients will be randomly assigned to receive Lactocare (ZistTakhmir) capsules 500 mg every 12 h or a placebo capsule, which contains only the sterile maize starch and is similar to synbiotic capsules for 14 days. The synbiotic and placebo capsules will be given through the nasogastric tube, separately from gavage, after feeding.

**Discussion:**

Gut microbiota modulation through synbiotics is proposed to improve clinical prognosis and reduce infectious complications, ventilator dependency, and length of ICU stay by improving energy and macronutrient homeostasis and reducing muscle protein catabolism.

**Trial registration:**

Iranian Registry of Clinical Trials, IRCT20190227042857N1. Registered on 17 March 2019.

## Background

### Gut microbiota, dysbiosis and critical illness

The gut microbiota refers to the commensal microorganisms that reside in our gastrointestinal tract (GIT) with a symbiotic relationship [1]. Gut microbiota has a significant role in host metabolism and homeostasis [2, 3]. A disturbance in this microbial community, which leads to an unhealthy state, is called dysbiosis [4]. Over the past decade, emerging evidence has demonstrated the role of intestinal dysbiosis in the pathogenesis of various conditions, such as infectious, immune, and metabolic diseases [5], while it has not been studied extensively in critical illness. An extreme and persistent dysbiosis occurs among critically ill patients, regardless of the heterogeneity of disease. The extreme dysbiosis in patients under critical care is due to the stress of critical illness, multiple antibiotics and additional pharmacological interventions, and highly processed enteral/parenteral nutrition [6, 7]. Dysbiosis in critically ill patients may make them prone to hospital-acquired infections, sepsis, multi-organ failure (MOF), energy homeostasis disturbance, muscle wasting, and cachexia [6, 8, 9].

### Dysbiosis and energy homeostasis in critical illness

The majority of patients in the intensive care unit (ICU) have had a severe illness, trauma, or major surgery, and accordingly they are unable to manage their nutritional demands. Although nutritional support is a daily practice in the ICU, many patients still suffer from malnutrition due to lack of intake or uptake of nutrients [10]. The prevalence of malnutrition in the ICU within developed and developing countries is reported as 50.8% and 78.1%, respectively [11]. Malnutrition is independently associated with longer ICU stay, more ICU readmissions, and a higher incidence of infections and risk of mortality [11]. A greater degree of malnutrition is also associated with a higher risk of 28-day mortality [12]. Malnutrition further tends toward acute or chronic loss of muscle bulk and function [13]. The gut microbiota and their derived metabolites play an essential role in the absorption, storage, and consumption of energy derived from the diet [14, 15]. Previous studies suggest that modulating gut microbiota by novel therapeutics, such as prebiotics, probiotics, or synbiotics, can have an effect on gastrointestinal tolerance and complications of enteral nutrition, which eventually lead to the regulation of energy intake. Recently, Tuncay et al. showed that enteric formula with prebiotic content in patients under neurocritical care was associated with a significant increase in total feed volume and energy intake and a non-significant tendency to achieve a target dose of nutrition more frequently and earlier [16]. Malik et al. also found that in patients in the ICU, receiving enteral formula supplemented with probiotics led to a faster return of gut function (tolerated feeding of 80% of their estimated required calories for 48 h consecutively) [17]. However, Sanaie et al. demonstrated that daily energy and protein intake in patients receiving probiotic supplements on the ICU were not significantly different from the group receiving placebo [18]. In the critical care setting, diarrhea is the most obvious complication of enteral nutrition (EN), which is associated with the inadequacy of energy and macronutrient intake [16]. Previous systematic reviews have confirmed the significant benefit of probiotics in the reduction of diarrhea in hospital patients overall. But a recent meta-analysis focused on patients in the ICU found no benefit of probiotics in preventing or treating diarrhea [19]. Besides, in the dysbiosis state of critical illness, microbial products that reach distant organs like brain, adipose tissue, and liver, favor the development of immune-mediated diseases and metabolic alterations [20]. Gut microbiota metabolites like short-chain fatty acids (SCFAs) can also influence the immune system and host metabolism, which regulates energy homeostasis [20]. Thus, gut microbiota modulation may be beneficial in the regulation of immune and metabolic responses and energy homeostasis.

### Dysbiosis and muscle wasting in critical illness

Muscle wasting, characterized by loss of muscle mass and strength, is associated with negative health outcomes such as functional disability, greater risk of infections, delayed recovery, poor life quality, and mortality [21]. The gut microbiota have been reported to influence muscle metabolism. The molecular mechanisms of this gut-muscle axis remain to be identified. Gut microbiota influence amino acid bioavailability and are sources of different metabolites, such as conjugated linoleic acid, acetate, and bile acids, which modulate muscle metabolism [8]. Various pathogen-associated molecular patterns (PAMPs) activate the transcription factor nuclear factor kappa light chain enhancer of activated B cells (NF-kB) through toll-like receptors (TLRs) and modulate the production of proinflammatory cytokines, which can induce muscle atrophy [8] (Fig. 1).

**Fig. 1 Fig1:**
[figure not shown]
Dysbiosis and muscle wasting in critical illness. Abbreviations: EN, enteral nutrition; IL6, interleukin 6; LPS, lipopolysaccharides; NF-kB, nuclear factor kappa light chain enhancer of activated B cells; PAMPs, pathogen-associated molecular patterns; SCFAs, short-chain fatty acids; TLR4, toll-like receptor 4; TNFα, tumor necrosis factor alpha

Modulation of gut microbiota through prebiotics, probiotics, or synbiotics can be considered as a potential treatment for muscle wasting and cachexia. In mouse models of leukemia, restoring Lactobacillus species by oral supplementation with *Lactobacillus reuteri* 100–23 and Lactobacillus gasseri 311,476 reduces inflammatory cytokines and expression of muscle atrophy makers [22]. In another study, Bindels et al. showed that prebiotic supplementation in leukemic mice could contribute to delaying anorexia and fat mass sparing by inducing a metabolic shift in adipose tissue [23]. In the mouse models of cancer cachexia, administration of a synbiotic supplement including inulin-type fructans and live *L. reuteri* 100–23 was associated with restoration of the gut barrier and immune function, thus reducing cachexia. It also prolonged survival [24]. Varian et al. also showed that probiotic administration in leukemic mice could inhibit cachexia by reducing systemic inflammation [25].

### Study rationale

Considering the extreme dysbiosis in critically ill patients and related energy and macronutrients homeostasis disturbance and muscle wasting, prompted us to evaluate the effect of synbiotic supplementation on the elimination of this condition. To our knowledge, this is the first study to investiage the effect of synbiotic supplementation on muscle wasting in critically ill patients.

## Study objectives

### Primary objective

The primary objective is to evaluate the effects of synbiotic supplementation on energy and macronutrient homeostasis and muscle wasting in patients under critical care.

### Secondary objectives

The secondary objective is to evaluate the effects of synbiotic supplementation on infectious complications and length of hospital and ICU stay in patients under critical care.

## Study design

This is a prospective, single-center, double-blind, parallel randomized controlled trial that will be conducted in Edalatian Medical ICU, Emam Reza Hospital, Mashhad, Iran. The study protocol was written following the Standard Protocol Items: Recommendation for Interventional Trials (SPIRIT) Checklist (Additional file 1).

## Selection and enrollment of participants

### Inclusion criteria

Participants must meet all the inclusion criteria to participate in this study: adults aged 18–65 years; admitted to the ICU; hemodynamically stable within 24–48 h after admission; requiring exclusive enteral nutrition (EN) via a nasogastric tube (NGT); not taking any kind of microbial cell preparations (prebiotics probiotics, synbiotics); estimated length of ICU stay more than 14 days; and provision of written consent.

### Exclusion criteria

All candidates meeting any of the exclusion criteria at baseline will be excluded from study participation: pregnancy or lactation; any contraindication to EN; any contraindication to insertion of the NGT; receiving immunosuppressive treatment, radiotherapy, or chemotherapy; hematologic disease; acquired immune deficiency syndrome (AIDS); transplant recipient; known allergy to microbial cell preparations; cancer or autoimmune diseases; artificial heart valve or congenital heart valve disease; estimated length of ICU stay less than 4 days; gastric disease; or gastrointestinal tract (GI) tract surgery.

### Study enrollment procedure

Before the screening procedure, informed consent will be obtained from every participant who meets the inclusion criteria. First, we will describe the purpose of the study, the procedures involved, the length of time the subject is suspected to participate, any possible disadvantages or discomforts, the benefits of the study to society and individuals, and the person to contact for answers to further questions. We will also emphasize that participation is voluntary, and refusal or withdrawal will not cause any loss of benefits that they are entitled to receive. Then the participants or their legal guardian will read and sign two copies of the written form. If, the informed consent was obtained from the patient’s guardian because of the patient’s lack of competence to consent and then later in the study the patient subsequently became competent as required, consent will be regained.

### Random allocation and blinding

After providing their written consent, patients are randomly allocated in a 1:1 ratio to the intervention or control group (A or B). Patients will be randomized through a stratified sequential randomization plan generated online. Randomization will be stratified by disease severity (Acute Physiology and Chronic Health Evaluation (APACHE) II,^1^ 0–35 and 35–70). For allocation concealment, we will use sealed opaque envelopes; inside each there is a carbon paper and the A or B card. To avoid probable selection bias, we will write the patient’s name on the envelope before opening it. All patients, researchers, and medical staff will be blinded to the allocation to either synbiotic or placebo capsules. An available third party, the secretary of the ICU, will be aware of whether A or B is allocated the synbiotic supplement. In the case of any complication associated with the intervention allocated, the medical staff will refer to the secretary for details.

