### Handling of the study intervention

The pharmaceutical company will provide synbiotic and placebo capsules in distinct boxes identified as A or B. Synbiotic capsules can be stored at room temperature for 2–3 weeks but the best condition for keeping this product is in the refrigerator at 2–8 °C. Unused study products will be returned to the company supplying them.

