### Adherence assessment

As the researcher will administer the capsules to the patients through the NGT, adherence assessment is not required.

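### Two arm-wide letters code every envelope and box, so disclosing one patient's treatment can expose the arm of every patient whose letter is known

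*Protocol article*

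**What the plan says.** Under Random allocation and blinding, patients are allocated 1:1 to group A or B. Of the concealment envelopes the section says "inside each there is a carbon paper and the A or B card". It then sets the blinding standard: "All patients, researchers, and medical staff will be blinded to the allocation to either synbiotic or placebo capsules".

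The next two sentences name the code holder and the route to the code: "An available third party, the secretary of the ICU, will be aware of whether A or B is allocated the synbiotic supplement", and "In the case of any complication associated with the intervention allocated, the medical staff will refer to the secretary for details".

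Handling of the study intervention puts the same two letters on the product: "The pharmaceutical company will provide synbiotic and placebo capsules in distinct boxes identified as A or B". Adherence assessment says who handles it: "As the researcher will administer the capsules to the patients through the NGT".

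The article describes no patient-specific kit number, no multiple codes per arm and no individual sealed code break.

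**The concern.** With one letter per arm, the key is a single fact that applies to everybody. An answer about one patient cannot be kept to that patient, because whoever knows that patient's letter then knows what both letters stand for. The protocol promises that researchers and medical staff stay blind, and in the same paragraph opens a route that can end this for more patients than the one who prompted the question.

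At stake are the assessments that leave room for judgement:

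- Under Description of evaluations, feeds are advanced according to bedside signs of intolerance and gastric residual volume. That drives calorie intake, and so energy homeostasis (first primary outcome). It also drives protein intake, and so nitrogen balance (second primary outcome).
- Among the secondary outcomes, feeding tolerance, infectious complications, pressure-ulcer grade, ventilator-dependent days and ICU stay all involve clinical judgement. ICU stay is also the outcome on which the trial was sized.

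**Working it through.** The plan states no figure for blinding or code breaks, so there is none to reproduce. The check is of the code structure, followed by an illustration.

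**Structure**

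1. Number of codes: two, A and B. The same letters appear in the group allocation, on the envelope card and on the product box.
2. Content of the key: which of the two letters is the synbiotic. This is what the ICU secretary is described as knowing.
3. Effect of one answer: if a patient with letter A is said to have received the synbiotic, then A is synbiotic and B is placebo. If the answer is placebo, the reverse follows. Either answer fixes both letters.
4. Reach: the trial has 40 patients (Abstract, Methods; 20 per group under Sample size and randomization, 2 × 20 = 40). With the two-letter code, one answer can reveal up to 40 of 40 assignments to a person who knows all the letters. With a separate code per patient, it reveals 1 of 40.
5. Who could combine key and letters: the researcher gives the capsules from lettered boxes and so can know each patient's letter. Medical staff are the ones who receive the answer. Both work in one medical ICU (Study design), and the code holder is that unit's own secretary.

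**Illustration of how likely a first request is**

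Input from the document: n = 40. Assumed, because the document gives no rate: a per-patient probability p of a code request, independent between patients.

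P(at least one request) = 1 − (1 − p)^40

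| Assumed p | (1 − p)^40 | P(at least one) | Expected requests, 40p |
|---|---|---|---|
| 1% | 0.669 | 33% | 0.4 |
| 2% | 0.446 | 55% | 0.8 |
| 5% | 0.129 | 87% | 2.0 |

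These are probabilities of at least one request. They do not measure bias, and they do not say how many people would learn the key.

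**Which outcomes are exposed**

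Of the eight numbered primary outcomes, energy homeostasis depends directly on feeding. Nitrogen balance combines recorded protein intake with a laboratory measurement. The other six are laboratory measurements: 3-methylhistidine, its ratio to creatinine, free glycerol, glucose and insulin, CRP and neutrophil/lymphocyte ratio, and endotoxin. Bedside judgement enters mainly through the first two and through the clinical secondary outcomes listed above.

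**The case against.** A reader might infer that the first complication unblinds the whole trial, and that a break is close to certain because complications are frequent in intensive care. The documents support neither.

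- **Trigger.** It is limited to complications associated with the allocated intervention, a narrower set than ICU complications in general. No rate is given. Safety assessment describes ample evidence of safety and keeps high-risk patients out. This stands. The same section does name bacteraemia as the main risk, and adverse events are recorded daily, so a request is foreseeable even though its frequency is unknown.
- **Who is unblinded.** A person needs both the key and the patients' letters. The protocol does not say that the researcher is told the answer, that medical staff know other patients' letters, or what the details supplied by the secretary consist of. Spread of the key within one unit is plausible but inferred. This stands, and it makes exposure of all 40 patients an upper limit.
- **Timing.** Assessments already recorded cannot be biased by later knowledge. Post-allocation assessment closes on day 15 in Table 1, apart from outstanding length of stay and 28-day mortality. The patients at risk are those enrolled or still under assessment when the break occurs. This stands.
- **Outcomes.** Most primary outcomes are laboratory-based, and feed advancement follows a stated rule on intolerance signs and residual volume. This limits the damage without removing it: judging intolerance is still a bedside decision, and differences in co-intervention could reach laboratory values too.

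None of these points removes the structural weakness. The letters, the code holder and the disclosure route are stated rules, and nothing elsewhere in the document confines an answer to one patient. They are not details that an analysis plan would settle.

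**Conclusion.** The concern holds as a structural risk to blinding. The plan fixes a single two-letter key for all patients together with a disclosure route open to medical staff, so one answer that reveals a patient's treatment reveals the meaning of both letters. That undercuts the statement that researchers and staff remain blind.

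The firm part of the size is the contrast between up to 40 of 40 assignments and 1 of 40, which needs no assumed rate. The 33% to 87% range rests wholly on assumed, independent request rates of 1% to 5%. The reach beyond the people directly told rests on the key spreading within the unit. The document does not show that a break has occurred or that any result is biased. Confidence is high for the code structure and moderate for the consequence. The change is worth making because it is cheap and removes the weakness for patients still to be randomised.

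**What to change.** For patients not yet randomised:

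- Have the supplier, or another party outside the blinded team, label kits by randomisation number with no arm letter.
- Put the kit number, instead of a letter, in the envelope.
- Give the code holder a list by number, and have that person disclose only the requested patient's assignment. Staff can still ask whenever the protocol now lets them.

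For the whole trial:

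- Log each break with its date and who was told.
- Report breaks to date, with the outcomes assessed after each one.

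The cost is relabelling the remaining kits (at most 40) and keeping a code list, done by someone who may know the arms. Trial status gives a recruitment start of 1 March 2019, expected completion by October 2019, recruitment still ongoing at submission, and a protocol version dated 15 January 2020. Relabelling may therefore help only a few patients. Logging and reporting breaks remains useful at any stage.

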## Study interventions

### Interventions, administration, and duration

All eligible patients will receive standard hospital gavage as EN through the NGT in the 24-48 h after admission to the ICU. According to the recent European Society of Parenteral and Enteral Nutrition (ESPEN) guideline on clinical nutrition in the ICU [26], continuous rather than bolus EN is preferred because it causes less diarrhea, but there is no difference in other outcomes. Another systematic review showed that bolus feeding is associated with lower aspiration rate and better calorie attainment [27]. It also provides a greater stimulus for protein synthesis [28]. Considering these data and the availability of bolus EN in our hospitals we applied this method. In the absence of an indirect calorimeter, the simple weight-based equation of 20–25 Kcal/kg/day in the acute flow phase and 25–30 Kcal/kg/day in the anabolic flow phase is preferred for measurement of calorie requirements. For overweight and obese patients, ideal body weight: 0.9 × height (cm) − 100 (male) (or − 106 (female) is suggested as a reference weight [26]. To avoid overfeeding, the EN target will be prescribed within 3 days in patients with high nutritional risk and within 7 days in patients with low nutritional risk according to the modified Nutrition Risk in Critically Ill (NUTRIC)^2^ score. The flow charts in Figs. 2 and 3 will be used for initiation and continuation of EN.

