### Description of evaluations

As shown in Fig. 2, calorie achievement goals are set according to the patients’ modified NUTRIC score. In everyday visits, we will evaluate GI signs and symptoms (e.g. vomiting, diarrhea, abdominal distention) and gastric residual volume (GRV). If there is no sign or symptom of intolerance and GRV is less than 250 ml, EN will be increased by 10%. Otherwise, we will approach as shown in Fig. 3. Energy homeostasis (calorie intake-estimated calorie requirement) will be recorded each day. Mid-arm circumference, which is an available anthropometric measurement tool, will be evaluated twice a week. As all patients receiving EN should be monitored for some clinical and laboratory variables, we set our monitoring approach as reported by Berger MM, et al. [34], Monitoring nutrition in the ICU, Clinical Nutrition (2018). Concomitant medications, pressure ulcers, infectious complications, and other adverse events will be recorded every day. The APACHE II and Sequential Organ Failure Assessment (SOFA) will be scored on days 0, 8, and 15. Before and after the intervention, fasting blood and 24-h urine samples will be obtained. Urine urea nitrogen, 3-Methyl histidine, and creatinine will be measured in urine samples. Fasting blood glucose, insulin, C-reactive protein (CRP) and endotoxins will be measured in fasting blood samples.

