### Sample size and randomization

We did not find any similar study that has evaluated our primary objectives. So, we considered one of the main secondary objectives to estimate the required sample size. Mahmoodpoor and co-workers [35] reported the ICU stay in two study groups as 18.6 ± 8 and 11.6 ± 6.3 days. Considering alpha error of 0.05 and power of 80%, the required sample size allowing for 10% dropout is 20 patients in each group.

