### Outcomes

#### Primary outcomes

The primary outcomes are
Energy homeostasis (calorie intake-estimated calorie requirement)Protein catabolism (nitrogen balance)
Nitrogen balance is a measure of the net change in total body protein. It is the difference between nitrogen eliminated from the body and nitrogen ingested in the diet. A positive or neutral nitrogen balance shows that protein stores are increased or maintained, while a negative nitrogen balance indicates protein mass is decreasing. The practical method for estimating nitrogen balance supposes that total nitrogen loss is equal to urinary urea nitrogen excretion plus 4 g/day additional loss from non-urinary urea nitrogen, gastrointestinal, and insensible losses [36, 37]. To measure the nitrogen balance, during the 24-h urine collection, the total intake of protein will be recorded to calculate nitrogen intake: 24-h urine samples will be immediately delivered to the laboratory to measure urea nitrogen.
3.Muscle protein degradation (3-methyl histidine (3MH) in 24-h urine)
3MH is exclusively found in muscle proteins, and after protein degradation, it is rapidly excreted in the urine without further reutilization or metabolization. So, measuring urinary 3MH, after at least 1 day of a meat-free diet, can be used as a biomarker of muscle protein breakdown [38, 39]. After a 1-day meat-free diet, 24-h urine will be collected. Urine samples will be centrifuged for 20 min at 1000×g. The supernatant will be collected and stored at − 70 °C for a maximum of 2 months. The ELISA method will be used for 3MH detection.
4.Muscle protein turnover (3MH/creatinine ratio in 24-h urine)
Since 24-h urinary creatinine estimates the total pool of muscle proteins, muscle protein turnover can be calculated from the 3MH/creatinine excretion ratio [38]. A 24-h urine sample will be delivered to the laboratory to immediately measure creatinine by the enzymatic method.
5.Lipolysis (free glycerol in serum)
Free glycerol is an important index of lipid metabolism. When the body uses stored fat as the energy supply, glycerol and fatty acids are released into the circulation. The absence of glycerol kinase in the adipocyte decreases triacylglycerol resynthesize and supports hepatic gluconeogenesis [40]. After obtaining the overnight fasting blood sample, the serum will be separated. The serum sample will be stored at − 70 °C for further measurement of free glycerol by enzymatic colorimetric method.

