### Data analysis

Data will be analyzed using SPSS for windows version 11.5 and MedCalc Statistical Software version 18.11.3 (MedCalc Software bvba, Ostend, Belgium; https://www.medcalc.org; 2019). Descriptive (frequency, percentage, mean, standard deviation) and inferential analysis (student *t* test, paired sample *t* test, repeated measures analysis of variance (ANOVA)) will be performed. Any covariates will be controlled by ANCOVA or binary logistic regression. All tests will be two-tailed and a *p* value <0.05 will be considered as statistically significant.

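### Primary outcome 1 is an unscaled kcal difference from a weight-proportional requirement, so body size adds variance unrelated to treatment, and no adjustment for it is committed to

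*Protocol article*

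**What the plan says.** Under Interventions, administration, and duration, calorie requirement comes from "the simple weight-based equation of 20–25 Kcal/kg/day in the acute flow phase and 25–30 Kcal/kg/day in the anabolic flow phase". It is therefore proportional to a reference weight. Overweight and obese patients get a height-based weight instead: "For overweight and obese patients, ideal body weight: 0.9 × height (cm) − 100 (male", with a different constant for women.

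Description of evaluations fixes the outcome: "Energy homeostasis (calorie intake-estimated calorie requirement) will be recorded each day". The same difference heads the list under Primary outcomes. Neither place gives a per-kg or percentage form.

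Under Data analysis, "inferential analysis (student *t* test, paired sample *t* test, repeated measures analysis of variance (ANOVA)) will be performed", followed by "Any covariates will be controlled by ANCOVA or binary logistic regression". No covariate is named. Randomisation is stratified by APACHE II only.

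**The concern.** The subtracted requirement grows with body size, so the size of a deficit in kcal reflects both how well the patient was fed and how large the patient is. The second part has nothing to do with the synbiotic. It widens the between-patient spread of a primary outcome in a 40-patient trial, and a chance imbalance in sex or weight moves the arm means for reasons unrelated to the product.

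The Background describes one cited ICU trial on the relative scale ("tolerated feeding of 80% of their estimated required calories for 48 h consecutively"), so the authors know a size-free measure. The sample size rests on length of ICU stay, so nothing in the plan shows that the first primary outcome has precision to spare.

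**Working it through.** **The plan's own figure.** ICU stay of 18.6 (SD 8) against 11.6 (SD 6.3) days gives a difference of 7.0 and a pooled SD of √((64 + 39.69)/2) = 7.20. The normal approximation gives 2 × (1.960 + 0.842)² × 7.20² / 7.0² = 16.6, so 17 per arm. The t distribution needs 18 (80.9% power), and 18/0.9 = 20. The stated 20 per group reproduces, but for a secondary outcome.

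**Effect of body size on the outcome**, at 25 kcal/kg and 65% fed:
- 50 kg: requirement 1250, intake 812.5, difference -437.5 kcal/day.
- 80 kg: requirement 2000, intake 1300, difference -700 kcal/day, which is 1.6 times as large.
- Chance imbalance: at the same 35% shortfall, an assumed 5 kg difference between arms in mean reference weight shifts the arm means by 25 × 5 × 0.35 = 44 kcal/day.

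**Power cost.** All inputs here are assumptions. Each patient contributes one summary value, compared between arms by a two-sided t test at 0.05 with 20 per arm. Let R be the requirement, with coefficient of variation c. Let A be intake divided by requirement, independent of R, with SD s. Let m be the mean fractional shortfall in the control arm. The outcome is D = R(A − 1), so

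Var(D)/mean(R)² = (1 + c²)s² + c²m²,

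against s² on the percentage scale. The treatment effect δ is set to give 80% power on the percentage scale, which is δ = 0.909s. The m² term is averaged over the two arms (m and m − δ).

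Example with c = 0.20, s = 0.15, m = 0.50:
- δ = 0.136, and the mean of 0.50² and 0.364² is 0.191.
- Variance = 1.04 × 0.0225 + 0.04 × 0.191 = 0.0310, so SD = 0.176.
- Standardised effect = 0.774 and power = 66.5%, a loss of 13.5 points.

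Points of power lost by the unadjusted kcal difference, for s = 0.10 / 0.15 / 0.20:

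| c | m = 0.10 | m = 0.30 | m = 0.50 |
|---|---|---|---|
| 0.10 | 0.6 / 0.5 / 0.5 | 3.0 / 1.4 / 0.9 | 8.2 / 3.7 / 2.1 |
| 0.17 | 1.7 / 1.4 / 1.4 | 8.3 / 4.0 / 2.6 | 20.8 / 10.1 / 5.9 |
| 0.20 | 2.3 / 1.9 / 1.9 | 11.2 / 5.5 / 3.5 | 26.6 / 13.5 / 8.1 |
| 0.25 | 3.6 / 3.0 / 2.9 | 16.6 / 8.4 / 5.5 | 35.5 / 19.8 / 12.2 |

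The value of c is itself uncertain. In one assumed mixed population (mean BMI 26) it is 0.21 for actual weight. With the height-based weight it is 0.24 if that formula is applied as printed, and 0.18 if 0.9 multiplies the whole difference.

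**Remedies compared**, by simulation (20,000 trials per setting, 20 per arm, s = 0.20):

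| Model | c, m | kcal, unadjusted | percent | kcal with ANCOVA on requirement |
|---|---|---|---|---|
| Intake scales, proportional effect | 0.20, 0.5 | 72% | 80% | 77% |
| Intake scales, constant kcal effect | 0.20, 0.5 | 70% | 83% | 78% |
| Intake does not scale | 0.20, 0.1 | 51% | 46% | 79% |
| Intake does not scale | 0.20, 0.5 | 51% | 63% | 79% |

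Over c from 0.10 to 0.25, the ANCOVA column stays at about 76 to 79% in all three models. When requirement is the covariate, adjusting intake minus requirement gives the same treatment estimate as adjusting intake itself. That is why it does not depend on how intake relates to body size.

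**The case against.** **ANCOVA is already listed.** The protocol allows it, and a covariate list may sit in an analysis plan that is not shown. This stands in part: adjustment is possible, and it recovers most of the loss. But the outcome scale is fixed in this document, and nothing here commits the comparison of that outcome to an adjustment for weight or requirement.

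**Energy balance is an absolute quantity.** It matches the stated objective, feeding tolerance is a separate secondary outcome, and the Background also cites results as feed volume and energy intake. This is a fair reason to keep kcal as the reported scale. It is no reason to leave body-size variance in the test.

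**Intake may not scale with requirement.** Feeding is advanced by 10% without saying of what, the flow charts are not shown, and the gastric residual threshold is a fixed 250 ml. This stands, and it is why the percentage scale is not the first choice here. When intake does not scale and shortfalls are small, percent does worse than the unadjusted difference (46% against 51% above).

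**Stronger readings that a reader might infer.** One is a definite power loss, such as 4 to 16 points. The documents give no weight spread, shortfall, SD, effect or power for this outcome, so no fixed figure follows. Another is that the percentage scale is always better, which the simulation contradicts. A third is bias: randomisation protects the comparison, and not stratifying 40 patients by weight or sex is ordinary.

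**Conclusion.** The concern holds as a matter of precision. The requirement formula and the outcome definition agree with each other, so there is no contradiction to reconcile, but together they put body size into the first primary outcome, and no adjustment is committed to.

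The size is conditional. With intake scaling with requirement and a coefficient of variation of about 0.17, the unadjusted test loses about 1 to 2 points at a 10% mean shortfall. At a 50% shortfall it loses about 6 points with a between-patient SD of 20 percentage points, 10 with 15, and 21 with 10. Across the whole grid the range is about 0.5 to 36 points, with the top reached only at the largest assumed spread of body size and the smallest SD. The 80% reference is also an assumption, because the protocol states no power for this outcome. The change is worth making because it is cheap, not because a large loss has been shown.

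**What to change.** State that the primary analysis of outcome 1 compares the arms on the kcal difference by ANCOVA, with the baseline estimated requirement (or reference weight) as a named covariate. Fix the covariate at baseline, because the kcal/kg factor changes between phases after randomisation. State how the height-based reference weight is computed, so that the covariate is reproducible. The cost is one sentence and one degree of freedom, and no new data are needed.

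An acceptable alternative is to test intake as a percentage of requirement and report the kcal difference descriptively. This gains a few points over ANCOVA if intake scales with requirement. It loses a few against even the unadjusted difference if intake does not scale and shortfalls are small (5 points in the example above). Choose one before unblinding.
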